## Abstract

**Background:**

Insomnia is a common sleep disorder for adults with depression, with major impact on their quality of life. Previous trials suggest that listening to music may be helpful in the treatment of sleep disturbances in healthy populations, including students and elderly. In addition, small studies with clinical populations of traumatized refugees, adults with chronic insomnia and adults with depression insomnia add to the evidence base. However, the impact of music listening in the treatment of depression related insomnia is not well documented.

**Objective:**

To examine the efficacy of music listening on sleep quality, symptoms of depression, and quality of life in adults with depression-related insomnia.

**Method:**

A single-center randomized controlled trial (RCT) in a two-arm parallel-group design is conducted and reported according to the CONSORT guidelines. The trial consists of an experimental group and a standard care control group. Both groups receive standard treatment for depression following Danish clinical guidelines in an outpatient psychiatry unit. The experimental group listens to music for a minimum of 30 minutes at bedtime for 4 weeks.

**Discussion:**

This trial will provide information on the efficacy of music intervention as a non-pharmacological intervention in the treatment of depression-related insomnia. This study will provide novel knowledge concerning music medicine as an evidence-based treatment for depression.

**Trial Registration:**

Clinicaltrials.gov. ID NCT03676491, registered on 19 September 2018.

## Background

Depression is a common health problem and an increasing global burden. WHO has found unipolar depression to be the third largest burden of disease globally in 2004 and is projected to rank first in 2030 [1]. A result of depression is the loss of social and cognitive functions and quality of life. One of the symptoms in depression is reduction in sleep quality (insomnia). Sleep disturbances associated with depression include difficulties in falling asleep and maintaining sleep. Cognitive behavioral therapy (CBT) is recommended in clinical guidelines as first-line treatment [2, 3]. Other treatment modalities for sleep promotion include sleep hygiene, physical activity, light therapy, relaxation techniques, music/nature sounds and acupuncture [4]. Resolving sleep disturbances in patients with active or previous depression is important as it may prevent worsening of symptoms and relapse of depression [1].

Music listening is widely used as a sleep aid [5]. This practice is supported by a recent Cochrane review concluding that music may be helpful in improving sleep quality in insomnia [5, 6]. The review underlines that the small sample sizes of the studies performed so far is a major limitation and concludes that there is a need for additional intervention studies concerning the effect of music listening on insomnia on specific populations, including patients with depression.

Moreover, a systematic review shows that music listening may reduce symptoms of depression in adults when the music listening is conducted regularly for more than 3 weeks [7]. It was reported that patients responded more when given a choice of music [5].

Giving a choice of music and offering a selection of music with a variety to meet individual preferences are both important factors highlighted in research [8, 9]. New research should offer a broad selection of calm music to meet these criteria [6].

Patient-selected music has a risk of being too stimulating (effect-evoking or too dynamic, i.e. increasing pulse and respiratory rate) [10]. Therefore, playlists designed purposefully by music therapists are more likely to have a sleep-inducing effect [8].

Music preference and culture have an influence on the music-listening experience. The perceived quality of the music depends on age, gender, preference, musical training, and cultural belonging [11]. Music listening is a complex experience that influences the individual in many ways, not strictly in relation to sleep and relaxation, but also in relation to wellbeing and sense of self [11]. An improved sense of wellbeing may positively affect the subjective feeling of restedness. The association between wellbeing and quality of sleep is known and reported in the literature [12].

This study aims to add knowledge into these domains, investigating wellbeing by quality-of-life questionnaires as well as subjective and objective measures of sleep quality.

### Feasibility study

We have carried out an observational feasibility study introducing music listening as a non-pharmacological intervention to improve sleep quality for patients with depression [13]. Outpatients diagnosed with unipolar depression and sleeping problems (*n* = 11) were asked to listen to music for at least 30 minutes before going to sleep every night for a period of 4 weeks. Music listening was provided by a sound pillow equipped with an mp3 player containing 10 playlists of 30–60 minutes of relaxing music with different music styles (classical, easy listening, pop, rock) based on the literature of receptive music therapy [14]. The study indicated signs of improved sleep quality [13]. However, the study lacked a control group.

### Rationale for a randomized trial

Effective treatment modalities are in demand to supplement existing treatment of insomnia in depression. The positive effect of music on sleep quality has been reported in a number of study settings with clinical and nonclinical populations [6]. This study contributes to the investigation of the efficacy of music listening in the treatment of depression-related insomnia by combining subjective measures (self-reported data) and objective measures (accelerometer). In addition, a new app with specially designed playlists makes a large selection of music available to meet individual preferences.

### Method – aim and hypothesis

The primary aim is to investigate the effect of music listening on sleep quality at 4 weeks follow-up. The secondary aim is to examine whether music listening is effective in reducing symptoms of depression and improving quality of life as well as improving sleep quality at 8 weeks follow-up in patients with depression-related insomnia.

#### The following hypothesis is tested

The controlled use of a sound pillow (Fig. 1) in combination with the Music Star app (Fig. 2) can serve as a sleep aid in reducing depression-related sleep disturbances.

**Fig. 1 Fig1:**
[figure not shown]
Selected solution-enabling music listening. A sound pillow is a pillow with small internal speakers. The sound pillow features a port through which to connect a player (Mp3/iPad/mobile phone). The user selects the music on the player. (Photo courtesy of Sound Oasis)

**Fig. 2 Fig2:**
[figure not shown]
The Music Star is an app developed for iPad to select music from a number of specially designed playlists. Each playlist is represented by a colored triangle forming a star. (Photo courtesy of Musikstjernen IVS)

#### Definitions

Music listening, music intervention, and music medicine refer to the use of music as an intervention without an active music therapist. In this protocol, music listening implies listening to pre-recorded music.

Insomnia, sleep disturbances and sleeping problems refer to a broad understanding of the disorder. Symptoms include difficulties initiating and maintaining sleep.

The study is named MUsic STAr For Insomnia (MUSTAFI).

### Trial design

A single-center randomized controlled trial in a two-arm parallel-group design is conducted from May 2018 to December 2019 following the revised Consolidated Standards of Reporting Trials (CONSORT) guidelines [15]. The RCT includes two groups of participants, an experimental group and a waitlist control group. Both groups receive standard treatment for depression following national guidelines.

The duration of the intervention is 4 weeks. The participants are followed for 8 weeks. Participation takes place in the home of the patient. In addition, three scheduled visits to the hospital in relation to the research project are required. Baseline assessment is performed on the starting day. Follow-up measurements are performed after 4 and 8 weeks (Fig. 3).

**Fig. 3 Fig3:**
[figure not shown]
Flow diagram of MUSTAFI phases, including enrolment, allocation, follow-up, and data analysis

The black element in the bottom left of Fig. 3 illustrates the intervention given as an option to the waitlist control group. The participants may take home the sound equipment for 4 weeks. There is no data collection involved. This has been added to the study for ethical reasons and to limit drop out from the control group [16]. The schedule for the trial is described in the SPIRIT flow chart (Fig. 4) and the dimensions of the study protocol have been described, adhering to the SPIRIT checklist (Additional File 1).

**Fig. 4 Fig4:**
[figure not shown]
Schedule of enrolment, interventions, and assessments (Standard Protocol Items: Recommendations for Interventional Trials (SPIRIT) flow chart)

### Sample size

Based on a previous study, we assume that the mean decrease in Pittsburgh Sleep Quality Index (PSQI) scale is 3.04 (SD 2) points for the music intervention group and 2.04 (SD 1.67) points for the waitlist control group after 4 weeks of follow-up [17]. When estimating the sample size, we assume that 25% of the eligible patients will be willing to participate in the project. Based on the patient flow in the outpatient clinic and the available resources from the staff recruiting the patients, we assume that a total of 120 participants can be recruited over a period of 18 months. A dropout rate of 20% is expected. Hence, a total of 100 randomized patients are expected to complete the study. Based on the Satterwaite’s two-sample *t* test and with a total of 100 patients (*n* = 50 per group) the power of our study is estimated to be 76% (at a confidence level of 5%).

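### 120 recruited with 20% dropout leaves 96 completers (48 per arm), not the 100 (50 per arm) behind the stated 76% power

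*Protocol article*

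**What the plan says.** All of the relevant text is in the Sample size section of the protocol article.

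- Effect assumptions: "the mean decrease in Pittsburgh Sleep Quality Index (PSQI) scale is 3.04 (SD 2) points for the music intervention group". For the control arm, the assumed improvement over the same period is 2.04 points, with an SD of 1.67.
- Recruitment, set by patient flow and staff resources: "we assume that a total of 120 participants can be recruited over a period of 18 months".
- Attrition and its consequence: "A dropout rate of 20% is expected. Hence, a total of 100 randomized patients are expected to complete the study".
- Power: a Satterthwaite two-sample *t* test "with a total of 100 patients", 50 per group, at the 5% level, from which "the power of our study is estimated to be 76" per cent.

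The Randomization section gives 1:1 allocation. No other section gives a dropout rate or a recruitment target.

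**The concern.** The 100 is presented as a result: it is introduced by *Hence*, directly after the 120 and the 20%. Those two numbers do not give it. The next sentence then carries the 100 into the power calculation as exactly 50 per group, so the error passes into the published power.

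Two things are at stake. First, the expected number of completers is a figure against which retention will be judged. A trial that recruited exactly 120 and lost exactly 20% would appear to fall four short of its own expectation. Second, the power is what a reader will turn to if the result is null. It is already below 80% by the article's own account, and the slip makes it look slightly better than the stated assumptions allow.

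**Working it through.** **Inputs, all from the Sample size section unless noted**

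- Mean PSQI decrease: 3.04 (SD 2) with music, 2.04 (SD 1.67) in the waitlist group. Difference = 3.04 − 2.04 = 1.00 point.
- Recruited: 120. Dropout: 20%. Stated completers: 100, or 50 per group.
- Significance level 5%. The article does not say one- or two-sided; two-sided is assumed here and tested in step 1.
- Allocation 1:1 (Randomization section).

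**Step 1. Reproduce the stated power at 50 per group**

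SE = √[(2² + 1.67²)/n] = √[(4 + 2.7889)/50] = √0.13578 = 0.3685.

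Satterthwaite degrees of freedom = 95.0. Noncentrality = 1.00/0.3685 = 2.714.

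Two-sided power from the noncentral *t* distribution = **76.6%**, which matches the stated 76%. A one-sided test would give 85.3%, which does not match. The inputs, the method and the two-sided reading are therefore confirmed.

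**Step 2. Check the number of completers**

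| Question | Calculation | Result |
|---|---|---|
| Completers from 120 at 20% dropout | 120 × 0.80 | **96** (48 per group) |
| Dropout implied by 120 → 100 | 1 − 100/120 | 16.7% |
| Participants needed for 100 completers at 20% | 100/0.80 | 125 |
| A calculation that does give 100 | 120/1.2 | 100 |

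The last row suggests that 120 was divided by (1 + 0.20) instead of multiplied by (1 − 0.20). That origin is a guess; the mismatch does not depend on it.

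**Step 3. Power at the number the assumptions do give**

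At 48 per group, SE = √(6.7889/48) = 0.3761, degrees of freedom = 91.1, and noncentrality = 1.00/0.3761 = 2.659.

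| Per group | SE | df | Two-sided power | Difference detectable with 80% power |
|---|---|---|---|---|
| 50 | 0.3685 | 95.0 | 76.6% | 1.04 points |
| 48 | 0.3761 | 91.1 | 74.9% | 1.06 points |

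The change is 76.6 − 74.9 = 1.7 percentage points, or 1.1 points against the rounded 76% in print.

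**The case against.** No one can argue that 120 × 0.80 is 100. The case on the other side is about how much this matters and how exactly the correction can be stated.

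- **The effect is small, and no decision turns on it.** The 120 came from clinic capacity, not from a power target, and power is below 80% on either count. This stands. It limits the weight of the point, but it does not make the printed numbers right.
- **The text says recruited, not randomised.** The article attaches the word *randomized* only to the 100. Taking the 120 as the number randomised is the natural reading, because the Informed consent section places randomisation directly after consent and confirmation of eligibility, but it is an inference. It does not rescue the figure: 20% off 120 leaves 96 whichever label is used, and no second attrition figure is given.
- **Dropout is not timed.** Follow-up runs to 8 weeks, and the primary endpoint is at 4 weeks. If some participants leave only after week 4, more than 48 per group will have primary data, and power will be somewhat above 74.9%. This is a fair qualification. The article does not make that argument, however: it speaks of completing the study and uses the completers for its power.
- **The planned analysis is not a *t* test.** The Statistical methods section plans a mixed model with age and gender as covariates under intention to treat, so power from a *t* test is an approximation. That is true at 50 per group as well as at 48. The article's justification should still be consistent on its own terms.

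**Conclusion.** The concern holds. The article's own recruitment and dropout figures give 96 completers, 48 per group; the stated 100 is four too many. Power on the article's own method falls from 76.6% to 74.9%, and the difference detectable with 80% power rises from 1.04 to 1.06 PSQI points.

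The count of 96 needs no assumption beyond the stated 120 and 20%. The 74.9% assumes a two-sided 5% test, equal group sizes, the stated means and standard deviations, and that all of the 20% are lost before the week 4 assessment. This is a minor correction to a stated sample size and power, not a flaw in the design.

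**What to change.** Make the Sample size section consistent. Suggested wording:

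*With 120 participants randomised and 20% dropout, 96 (48 per group) are expected to complete the study. If all dropout occurs before the 4-week assessment, a two-sided Satterthwaite t test at the 5% significance level has about 75% power.*

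This costs a change of wording and a slightly less favourable power figure. Trial conduct is unchanged.

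If 100 completers are to be kept, the target should be raised to 125, which means five more participants than the clinic was assumed able to supply in 18 months. Restating the dropout as 16.7% would also balance the sum, but it fits the assumption to the desired answer and should be avoided unless there is evidence for that rate.

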### Setting and participants

The study will be conducted at a single study site: the Unit for Depression in Psychiatry at Aalborg University Hospital, Denmark. The participants are adult outpatients aged 18–65 years in treatment for unipolar depression in the Northern part of Denmark.

Patients are referred to the unit for depression with different backgrounds. Some patients have not previously been associated with psychiatry and are referred directly from private practice with moderate or severe symptoms of depression. Another group of patients are referred from an inpatient unit. These patients are in recovery and have a stabilized condition in need of follow-up treatment after discharge. A third group of patients have been diagnosed in previous contact or hospitalization and in need for treatment after a recurrent depression.

### Inclusion criteria

All patients are required to have a diagnosis of unipolar depression (ICD-10 Depressive singular episode F32 or Periodic depression F33) and sleeping problems identified by the Hamilton Depression Rating Scale (HAM-D) by a score of at least 2 of a single item or at least 3 in total for the three items (sleep items 4–6). In addition, the patients should receive treatment according to national guidelines for depression. This may include pharmacological treatment, psychotherapy, psycho education and electroconvulsive therapy. Participants are eligible if within age 18–65, in stabilized pharmacological treatment, and having at least 4 weeks of treatment.

### Exclusion criteria

Exclusion criteria are unipolar depression with psychotic episodes, substance or alcohol abuse, or sentence to treatment by law. Patients will be excluded if they have restless legs syndrome, obstructive sleep apnea, or other organic sleep disorders as well as hearing loss. In addition, patients with a dislike of music will be excluded.

### Recruitment

Patients are recruited in the Unit for Depression. Nurses, psychiatrists, and psychologists use the screening tool 4 weeks after the beginning of treatment or after medical treatment is stabilized. Participants are recruited through posters, information by doctors and word of mouth in the unit. After an initial assessment for eligibility, the patient is informed of the option to participate. The recruitment takes place during group meetings or during individual consultation in the unit. When the patient has declared an interest to participate, the psychiatrist of the patient fill out an inclusion document based on information from the patient journal and his/her knowledge of the patient. The document is forwarded to the research leader. If the patient is eligible, the music therapist makes an appointment to give detailed information on participation in the research project.

Patients are included according to the inclusion and exclusion criteria. The patient may be discharged during participation in the research project and finalize as a private person. If the increase in depression symptoms results in hospitalization, the patient may continue participation in agreement with caretakers in the unit. If the patient is changing medication but is interested in participation, the patient will be registered on a waitlist for inclusion.

### Informed consent

The patient may sign the informed consent after receiving oral and written information about the research project. The information explains the aim and the procedures of the research project, the use of sound equipment and accelerometer and the rights as a participant in a scientific health study. The patient has the option to ask questions and if the patient need time to consider the participation, the music therapist offer to call the patient after 1 week and a new meeting is set up for the signing of the informed consent. When the informed consent is obtained and the inclusion criteria are confirmed in the inclusion document, the music therapist proceeds with the randomization. An additional consent for collection and use of log file data from accelerometer and the Music Star app is signed after randomization. Documents of informed consent are kept in a securely locked place.

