### Randomization

Randomization takes place when the inclusion document has confirmed eligibility and the informed consent has been signed following the regulations of the The North Denmark Region Committee on Health Research Ethics Randomization is carried out by the use of REDCap (Research Electronic Data Capture) hosted at Aalborg University Hospital. REDCap is a secure web-based application designed to support data capture for research studies. The randomization will be stratified according to age, i.e., under 30 years versus 30 years and above. Randomization is performed using computer-generated block randomization (random block sizes 2–8) with 1:1 allocation between the intervention group and the waitlist control group.

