### Experimental intervention

The music intervention consists of listening to music with the use of a sound pillow, applying the music from the Music Star app with special designed playlists. The duration of music listening for 30 minutes minimum at bedtime is guided by previous studies [6]. The principal investigator [name] gives an oral guideline to music listening and use of sound equipment at the baseline appointment including how to adjust the volume. The pillow speakers allow audio listening at very low volume. Adherence to the intervention (30 minutes of bedtime music) is monitored through log file data from The Music Star app.

Instructions for the experimental intervention:
It is required that you listen to music of your choice from the Music Star for at least 30 minutes at bedtime every night for 4 weeks. You may use the Music Star during the night or in the early hours of the morning if you wake up and have difficulty falling asleep again.You may turn off the Music Star if you wake up when the music plays and it is disturbing.The music will automatically stop when the playlist ends after 30 or 60 minutes.You may use the Music Star in the daytime to assist a rest. It is important only to use the Music Star for relaxation and sleep.You are advised to listen to the different music available to select your preferred playlists. You may select a particular playlist to play every night. Some people find that it is helpful to let a specific piece of music be a signal for sleep initiation.Consider choosing music that you like and that may help you fall asleep.You have to listen to music at night in the way it is described for the research purpose, i.e. the sound pillow in combination with the Music Star app.You may listen to your own music during the daytime.

Instructions on the use of the sound equipment:
Place the sound pillow on your bed (remove your own pillow) and place the Music Star close to the bed on a small table or chair for easy access during the night.Make sure that you have recharged the Music Star during the day.If you have technical problems with the sound equipment, you may contact the research leader by phone from 9am to 12pm on weekdays.

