#### Waitlist control group

The participants in the waitlist control group are asked to continue their normal bedtime routines. They are not given any instructions concerning music listening during the 8 weeks. At the baseline appointment, they are informed of the option to take home the music equipment to test for 4 weeks at the end of the 8-week period.

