### Statistical methods

We initially perform a descriptive analysis on age, gender, medication, illness duration etc. The two groups are compared within groups and between groups using F-tests and chi-squared tests. Additionally, we compare the groups on outcome measures at baseline.

Data analysis for the RCT will be performed using mixed effects linear regression with subject specific random effects. The intervention group will be initially compared with the control group on change of all outcome measures after 4 and 8 weeks. Age and gender will be added as covariates in all regression analyses. Repeated-measures analysis of variance (RM-ANOVA) will be used to compare results from baseline follow-up one and follow-up two.

Finally, a descriptive analysis of the playlists is included in the study, i.e. analysis of playlist preferences (style, duration, time of day) in the group of patients benefitting most from treatment compared to the group of patients benefitting the least.

Blinding of the researchers performing the scorings before and after the treatment as well as the subjects of the study will not be possible. Patients will be anonymized when analyzing data. All main analyses will be carried out based on the intention-to-treat principle. Information on adherence is obtained from the Music Star log file data. Compliance rate will be part of the primary study publication.

In case treatment is associated with dropout rate, we will investigate differences in baseline characteristics between complete cases and patients that are lost to follow-up. Any baseline characteristics that are significantly different between these two groups will be used as adjustment parameters in a sensitivity analysis of music listening treatment on the primary outcome.

A multiple comparisons analysis will not be performed, since the results of the analyses of music listening treatment on secondary outcome are purely exploratory, in which case multiple testing analysis is less important [26].

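### Consent to accelerometer data is taken after randomisation, and the text leaves open whether the self-reported baseline is too, so both may depend on the allocated arm

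*Protocol article*

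**What the plan says.** **Trigger for randomisation.** The Informed consent section says: "When the informed consent is obtained and the inclusion criteria are confirmed in the inclusion document, the music therapist proceeds with the randomization". The Randomization section repeats the two conditions: "Randomization takes place when the inclusion document has confirmed eligibility and the informed consent has been signed". Neither lists baseline measurement as a step before allocation.

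**Accelerometer consent.** The Informed consent section continues: "An additional consent for collection and use of log file data from accelerometer and the Music Star app is signed after randomization". Under Secondary outcome measures, actigraphy is endpoints 2 and 3, the change from baseline at 4 and 8 weeks, compared between arms.

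**Baseline.** The Trial design section says: "Baseline assessment is performed on the starting day". The baseline appointment differs by arm. In the music arm the principal investigator "gives an oral guideline to music listening and use of sound equipment at the baseline appointment" (Experimental intervention). For the waitlist arm: "At the baseline appointment, they are informed of the option to take home the music equipment to test for 4 weeks" (Waitlist control group).

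**Blinding.** The Statistical methods section says: "Blinding of the researchers performing the scorings before and after the treatment as well as the subjects of the study will not be possible".

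**The concern.** There are two separate issues, and the evidence for them is not equally strong.

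**Actigraphy.** A participant who already knows the arm is asked whether accelerometer data may be collected and used. A waitlist participant has less reason to agree than one who has just received the music equipment. If refusal differs by arm, those with actigraphy data are no longer the randomised groups. The intention-to-treat principle does not restore that comparison, because the data are missing for a reason that arises after allocation. Late consent is natural for the Music Star log, which only the music arm generates during the 8 weeks. It is not needed for an outcome measured in both arms.

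**Self-reported and rated baseline.** The primary endpoint is the change in PSQI from baseline at 4 weeks. If baseline answers are given after the arm is known, any reaction to the allocation enters the endpoint directly. The same holds for WHO-5, WHOQOL-BREF and the unblinded HAM-D rating. Unblinded reporting at 4 weeks cannot be avoided in this design. Unblinded reporting at baseline can.

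**Working it through.** **Step 1. What the text fixes about the order.**
- Consent to accelerometer log data: after randomisation. This is explicit.
- Arm-specific information: at the baseline appointment. This is explicit for both arms, so the arm is known by the end of that appointment.
- Baseline questionnaires and HAM-D: on the starting day. Their place relative to allocation is not stated. Two sequences fit: (a) consent, allocation, then questionnaires and instructions; (b) consent, questionnaires, allocation, then instructions. The two-condition trigger and the remark that scoring before treatment cannot be blinded lean towards (a), but do not establish it.

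**Step 2. Reproduce the protocol's power.** Inputs from the Sample size section: mean decrease 3.04 (SD 2) against 2.04 (SD 1.67), difference 1.00, 50 per group, 5% level, taken as two-sided.
- SE = √(2²/50 + 1.67²/50) = √(6.7889/50) = 0.368.
- Satterthwaite df = 95.0; noncentrality = 1.00/0.368 = 2.71.
- Power = 76.6%, against 76% stated. It reproduces. One-sided 5% would give 85.3%, so the two-sided reading is right.

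**Step 3. How a baseline shift enters.** Let D = (baseline − week 4 in music) − (baseline − week 4 in waitlist). A between-arm shift b in reported baseline, with week 4 unaffected, changes D by b. The rejection rate is that of a noncentral t with noncentrality (true difference ± b)/0.368.

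| Assumed shift b (PSQI points) | Rejection rate, no true effect | Power, true effect 1.0, shift against music | Power, true effect 1.0, shift for music |
|---|---|---|---|
| 0 | 5.0% | 76.6% | 76.6% |
| 0.1 | 5.8% | 67.6% | 84.0% |
| 0.25 | 10.3% | 52.2% | 91.9% |
| 0.5 | 26.9% | 26.9% | 98.1% |

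The values of b are assumptions; the documents give none.

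**Step 4. Direction.** A higher PSQI is worse sleep. If waitlist participants report worse sleep at baseline after learning their arm, their later decrease grows, D falls, and the bias is against music. If music participants report better sleep at baseline out of optimism, their decrease shrinks, again against music. Almost all the excess rejections lie on the side of the shift: at b = 0.25, 9.9 of the 10.3 percentage points.

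**Step 5. Actigraphy.** If 0% refused in one arm and 10% to 20% in the other (assumed), 50 participants would remain against 50 × 0.90 = 45 or 50 × 0.80 = 40. The smaller group would have been selected after allocation. The loss of numbers is modest; the selection is the problem.

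**The case against.** The strongest objection concerns the baseline. A reader might infer that the protocol places randomisation before the baseline assessment. No sentence says so. The consent and randomisation sections give the conditions that permit allocation, which need not be every step that precedes it. Arm-specific instructions at the baseline appointment are equally compatible with questionnaires completed first in the same visit. The flow diagram and the schedule of assessments (Figs. 3 and 4), which might settle this, are not available, and the article condenses a fuller protocol. This stands: the baseline part is a suggestion from the text and a request for clarification.

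On the accelerometer, the information given before the main consent already covers its use, no refusals are reported, and the secondary outcomes are labelled exploratory. This lowers the stakes. It does not remove the point, because collection and use of the data still wait for a signature given after randomisation.

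On size, the shifts are assumed, and PSQI asks about the past month, which makes it less sensitive to the mood of the day. A reader might take the raised rejection rates as false claims for music. The likelier reactions bias against music, so lost power is the more natural consequence. A reader might also suppose that the model adjusts for a contaminated baseline covariate; Statistical methods names only age and gender. Baseline enters through the change score and the repeated-measures comparison.

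A 4-week comparison without baseline still rests on unblinded self-report and is not the defined primary endpoint. It can therefore serve only as a sensitivity analysis.

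**Conclusion.** The accelerometer point holds on the text: consent to an outcome measured in both arms is taken after allocation in an unblinded trial, so missing actigraphy can depend on the arm. The baseline point holds as a risk that the visible text leaves open, not as a documented order. Neither is a demonstrated bias.

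The size is illustrative. It rests on the protocol's SDs, 50 completers per arm, a two-sided 5% t test, and a shift that passes in full into the change score. On those terms 0.1 points does little harm, while 0.25 points, a quarter of the planned effect, roughly doubles the type I error or moves power to about 52% or 92%. The stated 76% power is not in question. The point is worth acting on because the remedy is nearly free and, at the last reported count, 42 of the planned 120 participants had been included.

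**What to change.** 1. Include collection and use of accelerometer data in the main consent, signed before randomisation. Leave only the Music Star log consent for after allocation.
2. State that the PSQI, WHO-5, WHOQOL-BREF and HAM-D are completed and entered in REDCap before allocation is generated and disclosed, with arm-specific information given afterwards. If this was already the practice, one sentence saying so is enough for the questionnaires and HAM-D; the accelerometer consent still has to move.
3. For participants already enrolled, record the actual order of baseline and allocation, and report actigraphy consent and missing data by arm.
4. If any baselines were taken after allocation, add a sensitivity comparison of 4-week PSQI between arms without the baseline, and report the order as a limitation.

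The cost is a small amendment to the consent form and a different order of steps within the same visit. No visit or questionnaire is added.
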